## Abstract

**Background:**

Total Knee Arthroplasty (TKA) is a common and generally effective procedure performed mainly due to advanced osteoarthritis, pain, physical disability and reduced quality of life. However, approximately 20% of the patients respond poorly to the surgery and chronic pain and disability following TKA remains a major health burden for many patients. Among the most well documented and powerful psychological predictors of poor outcome following TKA is pain catastrophizing. Recent research has shown that patients with these thoughts are at higher risk of having persistent pain and lower physical function after the operation than patients with low levels of pain catastrophizing before TKA. There is high need of developing treatments aimed at improving self-management for this group of patients and the aim of this study is to investigate the effectiveness of a patient education in pain coping on physical function and pain among patients with high pain catastrophizing score before a TKA.

**Methods:**

This study is a two-arm parallel group trial design including 56 patients with high levels of pain catastrophizing referred for total knee arthroplasty due to osteoarthritis. Patients eligible for participation will be randomized into the two arms, usual care or usual care and patient education. Usual care consists of operation and standard rehabilitation. The patient education consists of 7 individual sessions focusing on pain behavior and pain coping managed by a physiotherapist. Three before the operation and four after. Measurements will be taken at baseline before the operation and 3 and 12 months after the operation. Primary outcome will be pain after 12 months measured with VAS (Visual Analogue Scale). Secondary outcomes include physical function and activity, quality of life, pain management and psychological factors.

**Discussion:**

Only few studies have evaluated the effectiveness of psychological interventions on patients with high levels of pain catastrophizing before the operation. This trial will provide evidence for the effectiveness of a cognitive-behavioral patient education delivered by physiotherapists and may provide better functional outcome and less pain for a vulnerable group of TKA patients. We expect that the results can provide important new knowledge to the current care recommendations.

**Trial registration:**

Clinical Trials (NCT02587429). Registered 23 October 2015

## Background

Total Knee Arthroplasty (TKA) is a common and generally effective procedure and most of the operated patients have less pain and higher functional ability after the surgery [1]. However, some patients respond poorly to the surgery and chronic pain following TKA remains a major health burden for many patients [2]. “Poor” outcome following TKA is due mainly to disabling pain and impaired function [3, 4]. Thus, persistent knee pain was reported 12 months after TKA in 16.4% of the patients by Baker et al. who followed 9417 patient’ pain using the Oxford Knee Score (OKS) [3]. Similar pain results were reported by Nilsdotter et al. [5]. Most recently, in a systematic review Beswick and colleagues stated that 20% reported persistent function-limiting pain 6 months or more following a TKA, despite an apparently normally functioning prosthesis [4]. Routinely screening for patients at high risk for persistent pain after the surgery is suboptimal and not common practice [6]. This practice has potential to change because resent research shows that we are able to identify several psychological predictors of poor outcomes after knee arthroplasty. From the literature on non-surgical chronic pain the evidence suggests that pain disability does not result solely from the severity of pain but is largely influenced by patients’ adjustment and interpretation to their pain [7, 8]. Among the most well documented and powerful psychological predictors of poor outcome following TKA is pain catastrophizing [9]. Pain catastrophic thoughts are related to pain rumination, pain magnification and helplessness in the face of pain. New research has shown that patients with these thoughts are at higher risk of having persistent pain and lower physical function after the operation than patients with low levels of pain catastrophizing before TKA [2, 10–14].

Cognitive Behavioural Therapy (CBT) is one of the most widely accepted models in the field of pain psychology and the biopsychosocial approach of CBT focuses on the complex interaction between psychological (mood, personality, behavior, cognition etc.), social (cultural, familial, socioeconomic, medical, etc.) and biological (genetic, biochemical, etc.) factors. The biopsychosocial model assumes that health problems are hardly ever limited to just one domain of human experience but by multiple domains of human experience. CBT is a treatment that helps patients understand the thoughts and feelings that influence behaviors. CBT consists of a cognitive aspect and a behavioural aspect. The cognitive aspect is based on Becks cognitive model [15]: the way that individuals perceive a situation is more closely connected to their reaction than the situation itself. A person’s cognition has impact on their mood and emotions, their bodily reactions and their behavior. This is illustrated in Fig. 1. The second part of cognitive behavior therapy focuses on the actual behaviors that are contributing to the problem. The client begins to learn and practice new skills and one of the aims is to decrease maladaptive pain behaviors. The goal of CBT is to identify maladaptive thoughts and consequently change them into more realistic and constructive thoughts to modify feelings and behaviour and thereby the experience of pain [15, 16]. CBT protocols are typically delivered by psychologists but they are often not integrated into primary care where most of the patients are seen. It may be beneficial to use a single health care professional to deliver the patient education in pain coping and in connection with the operation where the patients meet the physical therapist several times. Potential advantages of using only one health care person may be a reduced overall cost to the health care system, increased opportunity of receiving the treatment and an experience of a more consecutive treatment because the patient has contact to fewer health care persons. Physical therapists have a history of teaching patients about pain and pain coping, and given their expertise with using physical treatments to treat patients pain and their experience in using the biopsychosocial approach in their treatment, physical therapists is a qualified choice to deliver a patient education in pain coping [17, 18].

**Fig. 1 Fig1:**
[figure not shown]
The cognitive triangle – The link between thoughts, feelings, physical reactions and behavior

Psychological interventions as CBT that train patients in pain coping produce significant reductions in pain and improvements in self-efficacy and psychological well-being in individuals with knee osteoarthritis (OA) [19–23]. However, there has been only been very few attempts to reduce pain by using a CBT approach in a population of patients with high preoperative pain catastrophizing score. In 2011 Riddle et al. published the results of a quasi-experimental study. They found that patients who had received training in pain coping skills had a greater reduction in pain and pain catastrophizing 2 months after TKA. Furthermore, they had a larger improvement in physical function measured with Western Ontario and McMaster Osteoarthritis Index (WOMAC) compared to patients in the control group [24]. On basis of this study Riddle et al. has published a study protocol describing a clinical randomized trial [25]. Since there have only been few studies evaluating the effect of psychological interventions on knee pain and no randomized controlled trials evaluating the effect on patients with high levels of pain catastrophizing, well designed randomized controlled trials to determine the effectiveness of such interventions are needed. Our study will supplement the trial from Riddle et al. but there will also be several differences i.e. the study from Riddle et al. will test a telephone-based pain coping skills training contrary to our study where the patients come to the hospital and meet a physiotherapist at all training sessions. Further, in our study a larger part of the sessions are placed preoperative instead of postoperative. There is need for studies examining how to improve care and treatment for patients with poor pain coping at high risk of chronic pain after the operation. Our study aims to target this need. Our primary aim is to investigate the effectiveness of a patient education in pain coping on pain among patients with high pain catastrophizing score before a TKA. The secondary aims of the study are to investigate the effectiveness on physical function, physical activity, quality of life and pain catastrophizing. We hypothesize that patients with high pain catastrophizing scheduled for TKA who participate in a patient education in pain coping will experience 1) lower pain intensity 2) a higher physical function 3) a higher self-reported quality of life 4) and a lower pain catastrophizing score after the operation than patients who do not participate in patient education.

## Methods/Design

### Design

This study is a single centre double-arm parallel group design trial with 1:1 allocation with 1-year follow-up. Measurements will be taken at baseline before the operation and 3 and 12 months after the operation.

### Participants and recruitment

We will recruit 56 patients from the Orthopedic outpatient clinic at Holstebro Regional Hospital.

To be eligible for inclusion the patients must fulfill the following criteria:Be able to speak, talk and understand Danish language.Provide informed consent.Have a primary diagnosis of osteoarthritis.Be scheduled for an elective unilateral total knee arthroplasty.Age ≥ 18 years.A score >22 on the Pain Catastrophizing Scale (PCS).

### Exclusion criteria

Severe depression (at least three core symptoms and two accompanying symptoms) diagnosed with the Major Depression Inventory (MDI) [26].Scheduled for revision arthroplasty.Scheduled for a unicompartmental arthroplasty.Planning to have a contralateral knee arthroplasty within 1 year from the operation.Have a diagnosis of inflammatory arthritis.

Patients eligible for participation will be randomized into the two arms, usual care or patient education (Fig. 2). The patients will not be aware of the study hypotheses and will not be informed about the association between a high PCS score and long-term pain after TKA. The randomization will take place approximately 2–3 weeks before the operation. Because the time between the patients are scheduled for operation by the surgeon and the operation is very short (2–3 weeks) the patients will be randomized immediately after they are included and before baseline assessments to be able to make three pre-operative appointments with the patients in the intervention group.

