**Fig. 2 Fig2:**
[figure not shown]
Diagram of the patient flow through the study

Randomization will be conducted by permuted blocks and an independent staff will prepare consecutively numbered, sealed envelopes. The physiotherapists and nurses who execute the baseline and follow-up testing will be blinded for the randomization. The patients and the three physiotherapists delivering the pain coping education cannot be blinded.

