### Intervention group

The intervention group will in addition to the described usual care participate in a patient education based on cognitive-behavioral therapy. We wanted to design a patient education that fits into a hospital setting with relatively few session contrary to previous studies were the CBT intervention most commonly range from 10 to 12 sessions [20, 23, 29]. Our patient education consists of seven individual sessions. Three sessions before the operation and four after. A similar trial has recently shown similar amounts of sessions to be effective [24]. Except session one and three all the sessions will be in relation to the above mentioned planned visits at the hospital. The first session will be delivered approximately 2 weeks before the operation and the last one 3 months after the operation. Each session will be approximately 45 min in length. The patient education will be delivered by one of three physiotherapists with several years of experience in treating patients with TKA and a special interest in the CBT area. The three physiotherapists have participated in a 3-day training program delivered by two psychologists specialized in cognitive behavioral therapy and pain management. The patient education is developed together with the two psychologists and the three physiotherapists. The intervention is pilot tested on 3 patients with high pain catastrophizing score before we started including patients.

The same physiotherapist will follow the patient through all the 7 sessions. To make sure that the physiotherapists will all deliver the intervention in the same way they will be observed by each other on a regular basis.

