### Outcome assessment

The data presented in Table 2 will be measured before the operation and 3 and 12 months postoperative. Physical function and DXA scan will be measured during clinic visits. All the self-reported questionnaires are send by e-mail or post to the patients 2 weeks before the visit together with the tri-axial accelerometer. The primary outcome measure of the study is the 100-mm Visual Analogue scale (VAS), which is a self-reported pain measurement ranging from 0 indicating “no pain” to 100 indicating “worst pain imaginable” [31].

**Table 2 Tab2:** Primary and secondary outcome measures

Measure	Instrument	Collection points and method
Primary outcome:		
Self-reported Pain intensity	Visual Analogue Scale (VAS)	Baseline, 3 and 12 months follow up by post/email
Secondary outcomes:		
Self-reported function	SF-36 Physical Function	Baseline, 3 and 12 months follow up by post/email
Self-reported function and pain	Oxford Knee Score (OKS)	Baseline, 3 and 12 months follow up by post/email
Self-reported health status	EQ-5D-3 L	Baseline, 3 and 12 months follow up by post/email
Self-reported pain catastrophizing	Pain Catastrophizing Scale (PCS)	Baseline, 3 and 12 months follow up by post/email
Self-reported daily function and quality of life	Knee injury and Osteoarthritis Score (KOOS)	Baseline, 3 and 12 months follow up by post/email
Self-reported pain self-efficacy	Pain Self-Efficacy Questionnaire (PSEQ)	Baseline, 3 and 12 months follow up by post/email
Daily activity	Tri-axial accelerometer	Baseline, 3 and 12 months follow up by post/email
Physical function	6 min’ walk test (6MWT)	Baseline, 3 and 12 months follow up test in clinic
Physical function	Sit to stand 30 s. (STS30)	Baseline, 3 and 12 months follow up test in clinic
Muscle mass and bone mineral density	DXA scan	Baseline, 3 and 12 months follow up scan in clinic
Other measures		
Healthcare visits	Self-report (log book)	0–3 months’ post-operative at home
Smoking	Self-reported questionnaire	Baseline, 3 and 12 months follow up by post/email
Pain killers	Self-reported questionnaire	Baseline, 3 and 12 months follow up by post/email
Alcohol	Self-reported questionnaire	Baseline, 3 and 12 months follow up by post/email
Education	Self-reported questionnaire	Baseline, 3 and 12 months follow up by post/email
Social status	Self-reported questionnaire	Baseline, 3 and 12 months follow up by post/email

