There are some limitations as well. First, due to the different amount of attention paid to the patients in the two groups, a Hawthorne effect is possible [50, 51]. However, all patients will receive at least standard care which includes several contacts to both nurses, physiotherapists and doctors. Second, DXA scan, 30 s sit-to-stand and 6 MWT will be conducted after the first session in the intervention group. This procedure is chosen to be able to maintain the blinding of the physiotherapists by testing all the patients in the two groups the same day. However, the content of the first session is mostly introduction and since these outcome measures are not patient reported we do not think this will have an impact upon the results. Third, the patients will be randomized before baseline assessment. The reason for this is that the time between the patients are referred to a TKA and the operation is short and to be able to see the patients in the intervention group three times before the date for the operation this procedure is chosen. However, none of the patients are informed about the association between a high PCS score and long-term pain after TKA, so we don’t think this will affect the results.

We consider the external validity of the trial to be high while the treatment of TKA patients is almost similar all over the country. This makes it easier to implement at other Hospitals.

This project is expected to improve the overall treatment effect for a group of patients we today do not know how to treat the best way. We hope that this study can provide better functional outcome and less pain for the patients after the operation and that the study can produce new knowledge and inspire similar developments of interventions to other diseases.

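### Baseline VAS is self-reported after unblinded allocation, yet the stated primary contrast is measured from that baseline: a risk of bias that a cheap change of order removes

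*Protocol article*

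**What the plan says.** **Order of events.** Under Exclusion criteria, the protocol article says that "the patients will be randomized immediately after they are included and before baseline assessments", so that three pre-operative appointments can be booked. On the lead time it says: "The randomization will take place approximately 2–3 weeks before the operation". Under Intervention group: "The first session will be delivered approximately 2 weeks before the operation".

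**Blinding.** The paragraph after Fig. 2 states: "The patients and the three physiotherapists delivering the pain coping education cannot be blinded". Under Exclusion criteria there is a partial safeguard: "The patients will not be aware of the study hypotheses".

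**Collection.** Under Outcome assessment the primary outcome is a self-reported 100-mm VAS. The method is: "All the self-reported questionnaires are send by e-mail or post to the patients 2 weeks before the visit together with the tri-axial accelerometer".

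**Analysis.** Sample size and statistical analysis defines the primary outcome as VAS under activity at 12 months. It then describes between-group mean differences from baseline to 3 and 12 months, from a mixed model with time, group and their interaction.

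**Disclosure.** The Discussion lists randomisation before baseline as a limitation. It sets this aside because "none of the patients are informed about the association between a high PCS score and long-term pain after TKA". It separately says that DXA, sit-to-stand and the 6-minute walk follow session 1 in the intervention arm, and defends this on the ground that those measures do not come from patient report.

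**The concern.** A baseline value is safe to subtract because allocation cannot have influenced it. Here it can. A patient who has just learned that they will, or will not, receive pain-coping education then rates their own pain, and that rating becomes the reference point for the primary contrast. If knowing the arm moves the rating, the movement appears in the result as if it were treatment effect, with the sign reversed.

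The two defences in the Discussion do not reach this. Withholding the link between catastrophizing and later pain does not hide the arm. The argument about measures that are not patient-reported covers only DXA, sit-to-stand and the walk test; the primary outcome is patient-reported. At stake is the size of the primary estimate and, with it, power and type I error.

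**Working it through.** **1. The plan's own figure.** Inputs from Sample size and statistical analysis: difference 18 mm, SD 19 mm, alpha 0.05 (taken as two-sided), power 0.90.

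n per arm = 2 × [19 × (1.960 + 1.282) / 18]² = 23.4. The stated 23 is reproduced to within one patient (rounding up gives 24). Then 23 × 1.2 = 27.6, giving the stated 28 per arm. This basis is a difference at one time point with a between-participant SD, not a change score.

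**2. Timeline.** Randomisation is about 2–3 weeks before the operation and session 1 about 2 weeks before, a nominal gap of 0–1 week. Packs go out 2 weeks before a visit. The date of the baseline visit is not given; for the intervention arm it follows session 1. If it were about 1 week before the operation (assumption), packs would be due out 1 + 2 = 3 weeks before it. That is the day of randomisation for a patient with a 3-week lead, and before inclusion for a patient with a 2-week lead. So the completion date relative to session 1 is open. Completion after allocation is not open: the text states it.

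**3. How a shift passes through.** Let b be the mean shift in the intervention arm's baseline VAS caused by knowing the allocation, δ the true 12-month difference, and ρ the correlation between baseline and 12 months (equal SDs). The documents give neither b nor ρ.

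- Change from baseline estimates δ − b.
- Adjustment for this baseline (ANCOVA) estimates about δ − ρb.
- The 12-month difference alone estimates δ.

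With δ = −18 mm and ρ = 0.5:

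| b (mm) | Change from baseline | ANCOVA | 12-month difference |
|---|---|---|---|
| −5 | −13 | −15.5 | −18 |
| −3 | −15 | −16.5 | −18 |
| +3 | −21 | −19.5 | −18 |
| +5 | −23 | −20.5 | −18 |

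A simulation of 4,000 trials with 23 per arm agreed within 0.2 mm at b = −10, −5, 0, +5 and +10. For ρ from 0.3 to 0.7, a 5 mm shift leaves 1.5 to 3.5 mm of bias under ANCOVA.

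**4. Size against the target.** 3/18 = 17%; 5/18 = 28%.

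**5. Power and type I error of the change contrast** (23 per arm, ρ = 0.5, so SD of change = 19 × √(2 × 0.5) = 19). SE = 19 × √(2/23) = 5.60.

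- Power with no shift: Φ(18/5.60 − 1.96) = 0.895.
- b = −3: Φ(15/5.60 − 1.96) = 0.76.
- b = −5: Φ(13/5.60 − 1.96) = 0.64.
- Type I error with no true 12-month difference, 1 − Φ(1.96 − |b|/SE) + Φ(−1.96 − |b|/SE): 0.083 for 3 mm and 0.145 for 5 mm, in either direction.

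**6. Precision of the 12-month contrast.** Its SD is 19 mm whatever ρ is, so power at 23 per arm is 0.895. The change contrast has SD 19 × √(2(1 − ρ)): 22.5 mm at ρ = 0.3 (power 0.77) and 14.7 mm at ρ = 0.7 (power 0.99). The two are equal at ρ = 0.5.

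**The case against.** The order is disclosed and explained by the short lead time, and patients are kept unaware of the hypotheses. That safeguard is aimed at expectancy-driven reporting. It stands as a partial protection, but a patient who knows the arm can still rate pain differently.

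A reader might infer that the baseline VAS is completed after session 1. The documents do not say so. The Discussion names only DXA, sit-to-stand and the walk test as following session 1, and its defence of them suggests that the questionnaires come earlier. The point does not need that inference, because knowing the arm is enough.

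A reader might also infer that any analysis from the planned model is affected. It is not: the same model yields the 12-month group difference, which a uniform baseline shift does not move, and the primary outcome is defined at 12 months. But the contrast as worded runs from baseline, and that one takes the shift in full.

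Two further inferences fail. Patients without a baseline value are not excluded for that reason, since the mixed model uses whatever measurements exist. Nor does the plan list baseline VAS as a covariate, so misuse as a covariate is not something it proposes.

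**Conclusion.** The point holds as a risk of bias in the primary contrast as worded. Four elements are explicit: allocation before baseline, unblinded patients, a self-reported VAS, and a between-group difference taken from baseline. The size and direction of any shift are unknown. Lower baseline scores in the intervention arm would shrink the apparent benefit; higher ones, or lower scores in controls, would inflate it. The 3–5 mm range and ρ = 0.5 are assumptions, and the 17–28% follows from the first of these alone.

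It would go too far to say that the primary result is biased or the design invalid: this is a disclosed limitation for which the documents show a route to bias, not its occurrence. It is worth correcting because the remedy is cheap and a pre-allocation value not collected cannot be recovered later.

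**What to change.** 1. **Preferred.** At the outpatient inclusion visit, where the PCS is already completed, have each patient also complete the VAS under activity and the other short questionnaires before the envelope is opened. Use these, with the screening PCS, as baseline. The three pre-operative appointments can still be booked straight afterwards.
2. **If this is no longer possible.** State that the primary estimate is the 12-month between-group difference from the mixed model, without subtracting or adjusting for the post-randomisation baseline, and without constraining the arms to equal baseline means.
3. **Measures that stay after session 1** (DXA, sit-to-stand, 6-minute walk). Compare follow-up values between arms rather than change from that value. The same suits accelerometry, whose baseline also follows allocation.

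**Cost.** Option 1 takes a few minutes at an existing visit and a short amendment. Baseline questionnaires are then taken some days earlier, and in clinic rather than by post or e-mail; this applies to both arms alike. Because the PCS also selects patients, using the screening score as baseline brings regression to the mean into within-arm change, though not into the randomised comparison. Option 2 needs no change to visits, but loses precision relative to the change contrast if the baseline/12-month correlation exceeds 0.5.
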